## Abstract

**Background:**

Older adults with postlingual sensorineural hearing loss (SNHL) exhibit a poor prognosis that not only includes impaired auditory function but also rapid cognitive decline, especially speech-related cognition, in addition to psychosocial dysfunction and an increased risk of dementia. Consistent with this prognosis, individuals with SNHL exhibit global atrophic brain alteration as well as altered neural function and regional brain organization within the cortical substrates that underlie auditory and speech processing. Recent evidence suggests that the use of hearing aids might ameliorate this prognosis.

**Objective:**

The objective was to study the effects of a hearing aid use intervention on neurocognitive and psychosocial functioning in individuals with SNHL aged ≥55 years.

**Methods:**

All aspects of this study will be conducted at Swinburne University of Technology (Hawthorn, Victoria, Australia). We will recruit 2 groups (n=30 per group) of individuals with mild to moderate SNHL from both the community and audiology health clinics (Alison Hennessy Audiology, Chelsea Hearing Pty Ltd). These groups will include individuals who have worn a hearing aid for, at least, 12 months or never worn a hearing aid. All participants would be asked to complete, at 2 time points (t) including baseline (t=0) and follow-up (t=6 months), tests of hearing and psychosocial and cognitive function and attend a magnetic resonance imaging (MRI) session. The MRI session will include both structural and functional MRI (sMRI and fMRI) scans, the latter involving the performance of a novel speech processing task.

**Results:**

This research is funded by the Barbara Dicker Brain Sciences Foundation Grants, the Australian Research Council, Alison Hennessy Audiology, and Chelsea Hearing Pty Ltd under the Industry Transformation Training Centre Scheme (ARC Project #IC140100023). We obtained the ethics approval on November 18, 2017 (Swinburne University Human Research Ethics Committee protocol number SHR Project 2017/266). The recruitment began in December 2017 and will be completed by December 2020.

**Conclusions:**

This is the first study to assess the effect hearing aid use has on neural, cognitive, and psychosocial factors in individuals with SNHL who have never used hearing aids. Furthermore, this study is expected to clarify the relationships among altered brain structure and function, psychosocial factors, and cognition in response to the hearing aid use.

**Trial Registration:**

Australian New Zealand Clinical Trials Registry: ACTRN12617001616369; https://anzctr.org.au/Trial/Registration/TrialReview.aspx?ACTRN=12617001616369 (Accessed by WebCite at http://www.webcitation.org/70yatZ9ze)

**International Registered Report Identifier (IRRID):**

RR1-10.2196/9916

## Introduction

### Background

Aging is associated with the onset of postlingual sensorineural hearing loss (SNHL), which refers to hearing loss (or deafness) arising from the pathology of either the inner ear organs or the vestibulocochlear nerve after language acquisition. SNHL accounts for approximately 90% of hearing loss cases in adults and is insidious, progressing from normal (pure tone average [PTA]=0-25 dB) to mild (PTA=26-40 dB), to moderate (PTA=41-70dB), to severe (PTA=71-90 dB), and ending with profound (PTA >91 dB) or total hearing loss. However, more alarming are the sequelae of SNHL that might include rapid cognitive decline [1], impaired psychosocial functioning [2], increased risk of falling [3], and increased risk of incident dementia [4,5]. Recent work, including a meta-analysis of 33 studies [6], reported that SNHL is independently related to both cognitive impairment [7] and the risk of incident dementia [4] and perhaps, most critically, the degree of hearing loss predicts both the degree of cognitive impairment [1] and risk of dementia [4]. Furthermore, recent work suggests that 9% of dementia risk over the life course could be eliminated by avoiding the effects of hearing loss [5].

The scale of these problems is brought into sharp focus in the light of SNHL being the most prevalent chronic condition affecting older adults in developed countries (16%-20%) [8-10] and the second leading cause of years lost to disability globally [11]. Sadly, SNHL often goes undiagnosed and untreated or undertreated [12,13], and the sequelae of SNHL, incident dementia in particular, impose a significant burden not only on individuals and their families and friends but also on national health budgets [14,15]. A recent nationwide study in Australia found that all forms of hearing loss affected 14.5% of Australians (3.6 million people), especially those aged >50 years, with direct costs to the Australian economy of almost Aus $15.9 billion [16]. Furthermore, the number of Australians affected is expected to grow to 18.9% of the population by 2060, thereby slowing or stopping the progression of SNHL is a public health imperative.

The mechanisms underlying the links among cognitive decline, dementia risk, and SNHL are unknown but have been proposed to be due to either common neurodegenerative causes [17,18] or downstream neural changes precipitated by the diminished auditory input [1,19]. Core to these hypotheses is the theory that the diminished auditory input profoundly affects speech processing capabilities and consequently, impairs social functioning [12]. Consistent with these sequelae, individuals with SNHL exhibit accelerated brain atrophy compared with normal hearing adults, especially within right temporal lobe structures [20] that are critical for many cognitive functions. These findings are corroborated by reports that patients with SNHL exhibit atrophic and plastic alteration within cortical brain areas that underpin normal speech processing [21,22].

The initial stages of speech processing in normal hearing adults involve the analysis of basic speech sounds, including phoneme (speech sounds made by the mouth, eg, spoon has 4 phonemes; s/p/oo/n) and acoustic processing [23], which occur within the mid and posterior parts of bilateral dorsal temporal lobe structures, including the superior temporal gyrus, superior temporal sulcus, and planum temporale (for excellent review, see [24]). In their model of speech processing, Hickok et al suggested that subsequent higher-level processing, which includes motor (reproduction and planning) and memory (semantic and linguistic) processes and mapping of the initial sensory and phonological output onto the distinct dorsal and ventral neural pathways [24]. In addition, a left-lateralized dorsal articulatory motor network that includes the inferior frontal, premotor, anterior insula, and temporoparietal cortices maps the output onto articulatory representations; moreover, a bilateral ventral pathway that includes the anterior and posterior portions of the middle and inferior temporal lobes (sulci and gyri) map the output onto ventral lexical and semantic representations to facilitate understanding. Of key interest here are the alterations of brain structures that underlie speech processing in patients with SNHL.

Typically, individuals with SNHL adapt to their altered aural predisposition by relying increasingly on visual cues, including lip-reading. In normal hearing older adults, lip and word reading broadly activate the dorsal articulatory and spectrotemporal and phonological analysis networks mentioned above, except the primary auditory cortices due to the diminished auditory function [25]. Furthermore, SNHL adults engage in a similar network but exhibit higher amplitudes in the attendant structures, especially the prefrontal and premotor cortices, and recruit additional structures, including the right posterior temporal lobe [21,26-28], which is normally only activated by actual sounds [25].

**Figure 1 figure1:**
[figure not shown]
Hypothesized relationships associated with first-time hearing aid usage.

This functional alteration is thought to stem from the loosening of associations between memory and phonological processes and viseme (visual aspects of phoneme pronunciation) processes as SNHL progresses [29] (ie, altered functional connectivity), leading to these plastic brain changes. The phonological processing specialization of the left posterior temporal lobe appears to be preserved, whereas right lateral homologues that are predominantly involved in processing environmental sounds are repurposed to accommodate enhanced visual processing that aids the reading of visual cues (eg, lip-reading) and phonological processing capabilities [21,28,30]. Furthermore, the right anterior part of the superior temporal gyrus that normally performs voice and speaker identification functions is also repurposed for reading visual cues; however, this plastic alteration can be reversed by auditory rehabilitation [31].

Fortunately, a recent investigation suggests that hearing aids worn by individuals with SNHL can preserve or improve auditory and cognitive functioning [32-34] in addition to improving psychosocial well-being [33,35-38]. This suggests that stimulation, as afforded by hearing aid use, can preserve auditory functions and aural specificity and that hearing aids have a protective effect against the deleterious plastic alteration of auditory areas [39].

Alarmingly, however, approximately 90% of people with mild hearing loss, approximately 60% with moderate to severe hearing loss, and approximately 70% aged 65-84 years do not use hearing aids [40]. Furthermore, it often takes about 10 years for an individual to recognize that they have a hearing problem and then act, including obtaining hearing aids, to address this problem [41]. Critically, almost two-thirds of older adults with a hearing impairment do not use hearing aids [42].

This prospective cohort study, in which magnetic resonance imaging (MRI) is utilized in combination with clinical, neuropsychological, and hearing tests, aims to investigate the neurocognitive and psychosocial effects of wearing hearing aids in older adults with SNHL (ACTRN12617001616369).

### Study Objective

Through this study, we seek to understand whether the use of hearing aids can alter the neurocognitive function and affect beneficial plastic brain changes in individuals with SNHL. In particular, we aim to determine whether early intervention can normalize the function of the speech processing brain network. To this end, we will use neuropsychological, clinical, and psychophysical tests in combination with functional and structural MRI (fMRI and sMRI). In addition, fMRI acquisitions will include scanning during the performance of a speech processing task (detailed later) to probe the function of the speech processing network, besides the resting state fMRI to probe the brain network function more generally, whereas sMRI would enable the assessment of both the volume and integrity of the gray and white matter.

### Study Hypotheses

In comparison to the long-term hearing aid users, after wearing a hearing aid for 6 months, the group who have never worn a hearing aid will exhibit improved cognition, reduced depression, improved social interaction, altered activation of the auditory cortices and attendant networks, and altered connectivity between auditory and attendant networks.

In addition, the study will explore any baseline relationships among the cognition, psychosocial, and neural function in participants with and without a hearing aid and any relationships among the improved cognition, psychosocial function, and neural function in participants without a hearing aid after the hearing aid intervention, as seen in Figure 1.

## Methods

### Study Design

The study is a prospective cohort design evaluating the effect of the hearing aid use on cognition, psychosocial factors (eg, depression and social interaction), and neural function. We will recruit 2 participant groups of similar size consisting of people with mild to moderate SNHL. Of note, group randomization is not possible in this study; however, the groups will be matched as much as possible in terms of the degree of hearing loss.

Group A: Patients with SNHL who have used hearing aids for, at least, the previous 12 months and plan to continue using their hearing aids for the next 6 months.Group B: Patients with SNHL who have never used hearing aids before and who will be willing to wear hearing aids for the next 6 months.

All participants would be asked to complete, at 2 time points (t) including baseline (t=0) and follow-up (t=6 months), tests of hearing and psychosocial and cognitive function and attend an MRI session.

### Eligibility Criteria

Participants must be aged 55-90 years, speak English as first language, exhibit mild or moderate SNHL with a PTA of thresholds at 0.5-4 kHz in both ears, willing to undergo two 1-hour MRI scanning sessions over a period of 6 months, and willing to wear hearing aids for 6 months or must have been wearing hearing aids for at least 1 year. Furthermore, participants must give written informed consent.

Participants will be excluded if they exhibit left handedness, marked visual impairment that would prevent reading, cognitive impairment (defined as a score ≤23 on the Mini-Mental State Examination, MMSE), severe or profound hearing loss, and MRI contraindications. Figure 2 presents the flowchart of the overall data collection plan.

### Recruitment and Screening

Audiology health clinics with existing relationships with the Swinburne University, such as Alison Hennessy Audiology and Chelsea Hearing Pty Ltd, will be contacted to distribute the study promotional material to their clients who have previously undergone hearing assessments at the audiology clinic, been diagnosed with mild or moderate SNHL, and have been wearing their hearing aids for at least 1 year. In addition, the clinic will distribute promotional materials to clients who have recently been recommended to acquire hearing aids but have not yet decided to purchase the aids. All clients who express interest in the study through the audiology clinic will be invited to attend an information session at the Swinburne University of Technology.

**Figure 2 figure2:**
[figure not shown]
Data collection plan for experimental trial. APHAB: Abbreviated Profile of Hearing Aid Benefit; MMSE: Mini-Mental State Examination; MRI: magnetic resonance imaging; SUCCAB: Swinburne University Computerized Assessment Battery.

Participants who live within the Swinburne community will also be contacted by telephone and email by the researchers to explain the study; participants who express interest will be invited to attend the information session at Swinburne University. At the information session, the researchers will explain the purpose and significance of the study. At the same time, participants will complete a screening questionnaire to identify participants who will be willing to undergo hearing assessments, undergo two 1-hour MRI scans, and fulfill the inclusion criteria. Before completing the screening questionnaire, participants must provide verbal consent. Then, selected participants will be provided with a participant information and consent package for review, which will include further detailed information on the study procedure and a consent form. Participants willing to participate in the study will be scheduled for hearing assessment at the audiology clinics. At the hearing appointments, participants will submit their written consent before their hearing assessments, and those who meet the inclusion criteria will be scheduled to undergo their first MRI scan at a mutually convenient time at the Swinburne University of Technology.

### Study Power Analysis

With 30 consented participants in each group with a significance level of 5%, the power of 80%, and controlling for age, gender, and level of education, the baseline analysis of covariance (ANCOVA) model for spatial working memory performance can detect effect sizes of *d*=0.63 for between-group differences. Allowing 10% attrition in the 6-month follow-up period, a sample size of 27 in each group with a significance level of 5% and power of 80%, a significant group-by-time interaction effect can be detected for a large effect size of *d*=0.77. This study is based on the assumption that an effect size of *d*

### Intervention

#### Fitting of Hearing Aids in Group B Participants

Group B participants will be fitted with two demonstration hearing aids, known as Unitron Tempus Moxi Fit Receiver-in-the-ear hearing aids (Unitron, Kallang, Singapore). The hearing aids will be fitted by professional audiologists at the participating audiology clinics according to the best practice fitting guidelines including real ear (probe tube) measures to verify the amplification and match the appropriate prescribed amplification (typically using the NAL-NL2 prescription developed by the National Acoustics Laboratory [43]) with further adjustment and fine-tuning based on the users’ subjective preferences. In addition, the study audiologists will provide a pamphlet guide on the hearing aid use as take-home materials as well as a verbal explanation on how to use these hearing aids. Furthermore, postfitting support will be provided after 2 weeks to make sure that each participant is progressing with their hearing aids.

#### Follow-Up Periods After the Baseline Data Collection

During the 6-month waiting period between MRI scans, phone call and email reminders for the second testing session will be sent to all participants at 1, 3, and 5 months. At the same time, counseling and other compliance-improving policies [44-46] will be provided to ensure that participants are wearing their hearing aids. In addition, follow-up checks will be conducted by the audiology clinics every 6 weeks for first-time hearing aid users, during which hearing aid usage data will be downloaded and hearing aids will be restarted. An automatic internet-based data logging function installed in the hearing aids will be used to collect hearing aid usage data, which will be used to monitor and assess hours of hearing aid use by these participants. Furthermore, all participants will be encouraged to set their own goals for the hearing aid use and will be asked to assess how well these goals have been met on a regular basis.

#### After the 6-Month Follow-Up Period

All participants will return to the audiology clinics for further hearing assessments. Group B participants who received loaned hearing aids will return them. In addition, hearing aid supplier information will be provided to them if they are ready to purchase hearing aids. After hearing assessments, participants will return to the Swinburne University to complete the 6-month follow-up assessments.

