### Primary Statistical Analyses

In this study, repeated measures mixed model group (no hearing aid vs hearing aid users) x Time (Time 1 vs Time 2) analysis (RMMM) will be used for all analyses. The missing data will be accommodated in this analysis; however, in the case of whole-brain fMRI analyses, only completed protocol participants will be included. In the ITT RMMM analyses, the autoregressive (AR) dependence will be assumed.

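### As ordered, Group B appears to return its loaned hearing aids before the 6-month outcomes are measured, which does not fit the hypothesis or the follow-up section

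*Protocol article*

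**What the plan says.** All places are in the protocol article.

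- *After the 6-Month Follow-Up Period* gives the closing sequence. First, "All participants will return to the audiology clinics for further hearing assessments". Next, "Group B participants who received loaned hearing aids will return them", and supplier information is offered to those ready to buy. Finally, "After hearing assessments, participants will return to the Swinburne University to complete the 6-month follow-up assessments".
- *Study Design* lists what is collected at the second time point: "follow-up (t=6 months), tests of hearing and psychosocial and cognitive function and attend an MRI session". Group A consists of established users who "plan to continue using their hearing aids for the next 6 months"; no return step applies to them.
- *Fitting of Hearing Aids in Group B Participants*: "Group B participants will be fitted with two demonstration hearing aids", and the fitting is done at the participating clinics.
- *Study Hypotheses* sets the target: "after wearing a hearing aid for 6 months, the group who have never worn a hearing aid will exhibit improved cognition", relative to long-term users.
- *Follow-Up Periods After the Baseline Data Collection* treats the 6 months as the interval between the two MRI scans. Reminders, counselling and usage logging during it are meant to keep participants wearing their aids.
- *Primary Statistical Analyses* names the model: "repeated measures mixed model group (no hearing aid vs hearing aid users) x Time (Time 1 vs Time 2) analysis (RMMM").

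**The concern.** The hypothesis and the follow-up section imply that Group B is assessed as a group that has been wearing aids up to the second scan. The closing sequence implies that Group B is assessed after the aids have gone back. Group A's aid status does not change at that point.

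If the closing sequence is followed literally, current aid use at Time 2 differs by group. The group-by-time term then carries two things at once: 6 months of first-time use, and a period without aids in Group B only. The mixed model cannot separate them, because the unaided interval coincides exactly with being in Group B at Time 2. The contrasts exposed are those for SUCCAB (including the primary spatial working memory measure), DASS, SNI and MRI. Once the follow-up data are in, no analysis can restore the intended contrast.

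**Working it through.** **Order of events.**

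| Step | Group A | Group B | Source |
|---|---|---|---|
| During the 6 months | wears own aids | wears loaned aids, use logged | *Study Design*; *Follow-Up Periods After the Baseline Data Collection* |
| Clinic visit | audiometry | audiometry; loaned aids returned (by sentence order) | *After the 6-Month Follow-Up Period* |
| Interval to university visit | own aids | no loaned aids | length not stated |
| University visit | cognition, mood, social, MRI | same | *After the 6-Month Follow-Up Period*; *Study Design* |

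The hearing tests take place at the clinic visit and are unaffected. The baseline ANCOVA and ANOVA comparisons precede any loan and are unaffected.

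**The plan's own power figure.** Inputs from *Study Power Analysis*: 30 per group, 10% attrition, 5% significance, 80% power, detectable d=0.77 for the interaction. Sidedness is not stated; two-sided is assumed here. The interaction is treated as a two-group comparison on the d scale.

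- Attrition: 30 × 0.90 = 27 per group.
- Required n = 2(1.960 + 0.842)² / 0.77² = 15.70 / 0.593 = 26.5, so 27.
- Power = Φ(0.77 × √(27/2) − 1.960) = Φ(2.829 − 1.960) = Φ(0.869) = 0.81. With the noncentral t it is 0.79.

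The stated figure reproduces, and the design has no spare power at d=0.77.

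**Illustration of dilution.** This rests on two assumptions that the document does not supply: that the true effect is d=0.77, and that a share f of it remains when Group B is tested. Power = Φ(0.77f × √13.5 − 1.960).

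| Share kept, f | d at testing | Power, normal | Power, t | n per group for 80% (normal) |
|---|---|---|---|---|
| 1.00 | 0.770 | 0.81 | 0.79 | 27 |
| 0.90 | 0.693 | 0.72 | 0.71 | 33 |
| 0.80 | 0.616 | 0.62 | 0.60 | 42 |
| 0.75 | 0.578 | 0.56 | 0.55 | 48 |
| 0.50 | 0.385 | 0.29 | 0.28 | 106 |

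The first row is also the result if testing is on the same day and nothing is lost. The table shows sensitivity; it does not estimate a loss.

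**The case against.** The strongest reply is that the return of the aids at the clinic visit is inferred. The sentence about return gives no date or place, and the university session is tied to the hearing assessments, not to the return. The follow-up section points to wear up to the second scan. The data collection figure, not visible in the text at hand, may show the intended order, and visit windows are commonly left to a full protocol. This stands to the extent that the point is one of apparent order and inconsistency. It does not remove the point: the clinics fitted the aids, return is placed between the clinic visit and the university visit, and nothing in the text has Group B keeping the aids until testing is done.

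Several outcomes may also be insensitive to a short gap. Structural change built up over 6 months need not vanish in days, and SNI concerns 12 types of relationship. Scanner sound is delivered through headphones and adjusted to each participant's audiogram, so amplification during the speech task does not depend on holding the aids; only loss of daily use before the scan could matter there. All of this stands and limits the size.

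Group B was also unaided at baseline, so testing it without aids could be defended as holding its test-day condition constant. The article does not offer that rationale, and it would not account for an interval of unspecified length before testing.

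A reader might go further and infer that the plan fixes an open-ended withdrawal in Group B, or that power is really 55% or 28%. The document supports neither. An unstated interval is not an open-ended one. The shares lost are assumed, and d=0.77 is given as a detectable effect; the sentence on the assumed effect breaks off in the text available.

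**Conclusion.** The concern holds as an inconsistency with consequences for the main longitudinal contrasts. As ordered, Group B appears to give up its aids before the Time 2 cognitive, mood, social and MRI measurements, while Group A does not. This does not fit the hypothesis or the section describing support for wear between the scans.

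The contrasts at risk are the Time 2 group-by-time comparisons. The likely direction is dilution of any benefit that depends on current use, which works against the trial's own hypothesis. The size cannot be derived from the document. It could be negligible if both visits fall on one day, and it is smaller for task fMRI. The conclusion rests on reading the sentences of the closing section as a sequence.

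**What to change.** Reconcile *Study Hypotheses*, *Follow-Up Periods After the Baseline Data Collection* and *After the 6-Month Follow-Up Period* so that the Time 2 outcomes are measured before the loaned devices are collected. Specifically:

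- Keep audiometry first. That is the baseline order in *Recruitment and Screening*, and *Auditory Stimuli Input Considerations* sets the scanner sound from recorded audiograms. Moving the university session ahead of audiometry could leave the follow-up stimuli based on an audiogram about 6 months old.
- Collect the loan devices at the end of the university session.
- Record, for each Group B participant, the date of last use, and for everyone the interval between the clinic and university visits.
- If power under dilution is quoted, label it as illustration under the two assumptions above.

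The cost is a sentence or two in the protocol and two recorded items. Loan devices are out slightly longer and must be passed from the university back to the clinic. No extra visit is needed. The change has to be in place before follow-up testing, since it cannot be made in the analysis afterwards.
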